**Routine Arm (plus culture):**

2 sputum samples per patient.

- 1 sputum has standard smear microscopy at routine laboratory (either Paarl NHLS laboratory or on-site laboratory at Khayelitsha clinic).
- 1 sputum has microscopy and TB culture at reference laboratory (Greenpoint NHLS). Susceptibility will be done on clinical suspicion of MDR-TB

Treatment based on above results. Patients followed up at 2 and 6 months if they are smear or culture positive. Smear negative patients asked to return if symptoms persist. Smear negative, culture positive patients will be traced if possible.

**Xpert Arm (plus culture):**

2 sputum samples per patient

- 1 sputum for Xpert at routine laboratory
- 1 sputum for smear and culture at reference laboratory (DST performed if clinical suspicion of MDR-TB, or if Xpert test shows rifampicin resistance)

Treatment based on Xpert result, or culture result (in cases of Xpert negative, culture positive). Xpert or culture positive patients followed up at 2 and 6 months. Smear negative and Xpert negative patients asked to return if symptoms persist.

Phase 1 will allow us to evaluate the performance of the Xpert system in a clinic setting. The additional cultures performed will allow us to determine whether the performance of the assay in a routine setting is comparable to the performance described in a research setting. These are as described in Objectives 1b and 2a.

**Phase 2:** 16 weeks

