**SPECIFIC OBJECTIVES**

1. **Clinical performance**
   - Measure increased yield in TB and MDR TB case detection rates compared to local routine diagnostic algorithm
   - Determine sensitivity and specificity compared to central culture and DST (preferable on liquid media).
2. **Operational performance**

- Assess robustness of Xpert™ reagents and equipment, maintenance and customer support needs, as well as minimal training needs
- Develop recommendations on how to integrate automated molecular testing in resource – poor countries using existing diagnostic algorithms for case detection and MDR TB screening.

1. **Cost-efficiency**

- Quantify “per test” and “per patient” costs for the health system compared to routine culture and DST

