**Preparation and Participation of Health Services**

The proposed study will be cleared with the relevant clinic committees prior to commencing. The study nursing sister and medical officer will spend 2 weeks within the clinics prior to commencing to assess the best way of implementing the study without interfering with routine work, in consultation with the clinic workers.

The proposed study will be integrated into clinic activities so that it does not interfere with the routine activities of the clinics. We will aim to enhance clinic capacity in the following manner:

- 1. Patients will follow the normal flow within the clinic. Testing will be integrated into the routine activities of the clinic. We have received ethics approval for waiver of informed consent, since there is no risk and substantial benefit for the patients. There will therefore not be any additional time required for patient consent or information.
  2. We will provide one additional nursing sister or research worker per clinic as well as a clerical assistant / data capturer. These staff will assist with ensuring that records are complete, and that results are fed back to the relevant clinic staff in a timely manner. The only study-specific activities requiring additional health care worker time will be to ensure that the relevant data fields are captured. This will be performed by study staff. Study nursing staff will also contribute to the routine activities of the clinic, where the local clinic feels this to be appropriate.
  3. A study medical officer will be appointed. Part of his/her activities will include assisting with routine care of TB patients, where the local clinic feels this to be appropriate.
  4. The availability of GeneXpert results (with performance similar to that of TB culture) at the same clinic visit (or on the following day) will dramatically improve the ability to provide rapid and accurate diagnosis of tuberculosis at the clinics. Furthermore, identification of Rifampicin resistance will identify those patients at risk for MDR-TB. In all patients with a rifampicin resistant result, the test will be confirmed using Hain MTBDR*plus* testing for independent confirmation.

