Thus, participation in this project poses no foreseeable risk to patients. Furthermore, investigators will have no direct contact with patients. All data will be obtained from records collected by the clinical and laboratory staff and will be stripped of patient identifiers prior to entry into project databases. All study team members will be required to sign a confidentiality agreement that protects all patient information. No sample bank will be created. The stored pellets and culture isolates will only be needed to resolve discrepant cases. Finally, it must be ensured by all sites that patients diagnosed by Xpert™ MTB/Rif assay, including MDR TB cases, receive appropriate treatment according to program norms throughout the demonstration period.

Confidentiality: There are no risks with respect to confidentiality. Patient identifiers will be encrypted. Only authorized medical personnel at the study sites will have access to patient names.

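### In the Phase 1 Xpert arm the Xpert result partly decides who gets DST, so pooled rifampicin sensitivity is biased upward and specificity downward

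*Protocol*

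**What the plan says.** Under Specific Objectives, the second bullet of the clinical performance objective (cited later as 1b) reads "Determine sensitivity and specificity compared to central culture and DST". The last paragraph of the Phase 1 Xpert Arm section ties that objective to Phase 1: "These are as described in Objectives 1b and 2a".

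The rules on who receives DST are these:

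- **Phase 1 Xpert arm:** every patient has a reference culture, but for susceptibility the rule is "DST performed if clinical suspicion of MDR-TB, or if Xpert test shows rifampicin resistance".
- **Phase 1 Routine arm:** "Susceptibility will be done on clinical suspicion of MDR-TB". No Xpert is run here.
- **Phase 2 Xpert arm and Phase 3:** culture and DST follow only an Xpert result showing rifampicin resistance.
- **Preparation and Participation of Health Services:** "In all patients with a rifampicin resistant result, the test will be confirmed using Hain", so the line-probe confirmation has the same trigger.
- **Ethical Considerations:** "The stored pellets and culture isolates will only be needed to resolve discrepant cases".

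The benchmark for Phase 1 is in the section on clinical performance of the test. For rifampicin it gives a sensitivity of 96.1% and a specificity of 98.6%.

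**The concern.** The index test helps to decide who receives the reference test, which is partial verification. An isolate that Xpert calls susceptible, from a patient in whom nobody suspects MDR-TB, never enters the rifampicin table. If it is truly resistant, a missed case is absent from the sensitivity denominator. If it is truly susceptible, a correct result is absent from the specificity numerator and denominator. Xpert-resistant results, right or wrong, all stay in.

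Phase 1 is meant to show whether routine performance matches research performance. An upward bias in sensitivity could hide a real fall in the field, and a downward bias in specificity could suggest a problem that does not exist. The Aims section says that the data go to national authorities and WHO to inform policy.

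**Working it through.** **Is there another route to DST for the unverified cases?** None is written. The Routine arm produces no Xpert/DST pairs. Phase 2, Phase 3 and the line-probe step are all triggered by an Xpert-resistant result. Stored isolates are for discrepant cases, and an isolate that was never tested cannot be discrepant for rifampicin.

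**Inputs.** Se = 0.961 and Sp = 0.986 are the protocol's benchmark values. The protocol states no precision or sample size for rifampicin accuracy, so there is no planned figure to reproduce. The verified fractions are not given and are assumptions:

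- vR: fraction given DST among Xpert-susceptible cases that are truly resistant.
- vS: fraction given DST among Xpert-susceptible cases that are truly susceptible.

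**Formulas,** with all culture-positive Xpert-resistant cases verified:

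- Apparent sensitivity = Se / [Se + (1 − Se) × vR]
- Apparent specificity = Sp × vS / [Sp × vS + (1 − Sp)]

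**Results with vR = vS = v:**

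| v | Apparent sensitivity | Apparent specificity |
| --- | --- | --- |
| 1 | 96.1% | 98.6% |
| 0.5 | 0.961/0.9805 = 98.0% | 0.493/0.507 = 97.2% |
| 0.3 | 0.961/0.9727 = 98.8% | 0.2958/0.3098 = 95.5% |
| 0.1 | 0.961/0.9649 = 99.6% | 0.0986/0.1126 = 87.6% |

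Full verification (v = 1) returns the true values. Sensitivity depends only on vR and specificity only on vS. If suspicion is commoner in truly resistant cases, say vR = 0.5 and vS = 0.1, the pair is 98.0% and 87.6%.

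**Could a real fall be hidden?** Suppose that true field sensitivity were 80% (an assumption). At v = 0.2 it would appear as 0.80/(0.80 + 0.20 × 0.2) = 95.2%, and at v = 0.1 as 0.80/0.82 = 97.6%. Both look close to the 96.1% benchmark.

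**What is not affected.** The positive predictive value uses only Xpert-resistant cases, all of which are verified if culture-positive. TB-detection accuracy uses culture, which every Phase 1 Xpert-arm patient has.

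**Number of isolates.** Weekly alternation makes 8 of the 16 Phase 1 weeks Xpert weeks. With 45 to 50 suspects per site per week and two sites, 8 × 45 × 2 = 720 to 8 × 50 × 2 = 800 patients. At an assumed 20% to 30% culture-positive, that is 720 × 0.20 = 144 to 800 × 0.30 = 240 isolates. The Sample size section's total of 1600 to 1800 tests fits one site's load better (36 Xpert weeks × 45 to 50 = 1620 to 1800). On that reading the isolates halve to 72 to 120.

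**The case against.** The strongest case on the other side has four parts.

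1. **Xpert is not the only trigger.** Suspicion leads to DST whatever Xpert shows, and the inclusion criteria cover re-treatment cases, relapses, non-converters and symptomatic MDR contacts, so suspicion need not be rare. Follow-up at 2 and 6 months also records when drug resistance was diagnosed. This stands in part. A reader might infer that false-susceptible results can never be found, but the protocol does not support that: some will be found, and a large v makes the bias small. The direction does not change while v is below 1.

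2. **An unbiased subgroup exists.** Among suspected patients, DST does not depend on Xpert. This stands if suspicion is recorded before the Xpert result. The protocol does not fix that order, and the Study Sites section expects same-day results at Site B, so an Xpert result could influence suspicion. The estimate would also apply to that subgroup only.

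3. **An unseen SAP could restrict or correct the analysis.** Restriction, yes. Correction is harder. Under the written rule, an Xpert-susceptible patient without suspicion has no chance of DST, so inverse-probability weighting has nothing to weight. A Begg-Greenes correction would have to assume that resistance is as common among unsuspected Xpert-susceptible patients as among suspected ones. The SAP cannot supply DST results that the protocol does not generate.

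4. **Phase 1 may have been meant for TB detection only.** The text says "The additional cultures performed will allow us to determine whether the performance of the assay in a routine setting is comparable" and names cultures, not DST. But Objective 1b names DST and is assigned to Phase 1 without limit. If TB detection was all that was meant, the objective needs rewording.

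The Abstract also says that culture is done for all cases in the Implementation Phase, while the Phase 2 Xpert Arm section gives Xpert-negative cases no culture. These need reconciling, but neither promises DST for Xpert-susceptible cases.

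**Conclusion.** The concern holds for the rifampicin part of Objective 1b. As written, Phase 1 cannot give valid pooled rifampicin sensitivity and specificity. Any estimate pooled over the tested cases is biased upward for sensitivity and downward for specificity. The direction follows from the testing rule. The size rests on v, which the protocol does not give: at the benchmark values, between v = 0.5 and v = 0.1, sensitivity gains about 2 to 3.5 points and specificity loses about 1.4 to 11 points.

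Three stronger readings are tempting but not supported:

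- **That wrong figures will be reported.** This presumes a pooled, uncorrected analysis, which the protocol does not state.
- **That TB-detection accuracy is compromised as well.** Culture is universal in the Phase 1 Xpert arm.
- **That keeping isolates to resolve discrepant cases inflates accuracy.** The sentence stands in a paragraph on risk, confidentiality and sample storage. Nowhere does the protocol say that resolved cases are reclassified in the primary analysis.

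The weight is bounded too. The Study design section makes feasibility the primary purpose, and rifampicin accuracy is one part of one sub-objective. It still merits correction before Phase 1, because a stated objective is not met by the stated testing.

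**What to change.** **Preferred.** For accuracy purposes, do reference DST on all Phase 1 Xpert-arm culture-positive isolates, whatever the Xpert result. The isolates are already grown. The cost is laboratory work on about 144 to 240 isolates (two sites, 20% to 30% culture-positive), less those that would be tested anyway. This concerns the reference standard only; patient management is outside this point.

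This removes the bias but not the imprecision. At an assumed 5% to 10% resistance there would be about 7 (144 × 0.05) to 24 (240 × 0.10) resistant isolates, so sensitivity should be reported with its interval.

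Testing only a random fraction of Xpert-susceptible isolates is not a safe economy at this size. With 24 resistant isolates and an assumed sensitivity of 90%, 2.4 are missed by Xpert, and a one-in-four sample would expect to include 0.6 of them.

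**If no DST is added.** Amend Objective 1b so that rifampicin accuracy is limited to (i) the positive predictive value for resistance, and (ii) sensitivity and specificity among patients whose MDR suspicion was recorded before the Xpert result, labelled as applying to that subgroup. Do not report pooled sensitivity and specificity. The cost is a wording change, one dated data field for suspicion, and a narrower claim.

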**Routine Arm:**

2 sputum samples per patient

- 1 sputum for microscopy at routine laboratory
- 1 sputum for microscopy (routine laboratory), or microscopy plus culture +/- susceptibility testing (reference laboratory) at the clinic discretion (i.e., following standard practice)

Treatment based on microscopy and/or culture results, as per routine practice. Patients followed up at 2 and 6 months if they are smear or culture positive. Smear negative patients asked to return if symptoms persist. Smear negative, culture positive patients will be traced if possible.

**Xpert Arm:**

- 1 sputum for Xpert at routine laboratory
- 1 sputum for microscopy if Xpert positive, and for microscopy plus culture and DST if Xpert shows rifampicin resistance. The purpose of microscopy for the Xpert positive sputa is to provide a baseline microscopy result for follow-up purposes, as the national TB programme performs smear microscopy at follow up on smear positive cases. Xpert negative cases will have no culture performed.

Treatment based on Xpert results, Patients followed up at 2 and 6 months if they are Xpert positive. Xpert negative patients asked to return if symptoms persist.

Phase 2 is designed to assess the impact that introduction of the Xpert test will have on diagnosis and management of TB, as outlined in Objective 1a. Information from both this phase and phase 1 will be used to quantify the cost-effectiveness of the assay (Objective 3)

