## ETHICAL CONSIDERATIONS

During the various phases, patient management and TB treatment decisions will be based on either routine diagnostoic results, or the Xpert™ MTB/Rif results. For the Xpert results, the routine diagnostic algorithm will be modified. Ethical approval will therefore be obtained for all participating sites.

Benefits & Risks: Numerous published studies and a large-scale FIND demonstration project confirm the high accuracy of rpoB-based tests for rifampicin resistance detection. In June 2008, the Strategic Technical Advisory Group (STAG) of WHO has approved line-probe assays for MDR screening in developing countries. However, this use is restricted to central laboratories due to complexity and biosafety and equipment needs.

The Xpert™ MTB/Rif has the additional advantages of simplicity, reduced biosafety needs and much increased sensitivity which should allow using the assay for case detection in smear-negative patients as well as for MDR screening in decentralized settings. All results obtained so far have shown excellent assay performance.

Based on these results (as outlined in the Introduction), as well as on the fact the Xpert assay is currently licensed as a diagnostic test in Europe and has been recently introduced to the private sector in South Africa, we feel that the use of the Xpert assay to guide treatment decisions is justifiable and necessary, and that the use of the Xpert assay for a selection of patients provides at least as good a diagnostic test as the current standard algorithm (and probably a better diagnostic test). There is potential substantial benefit to participants in the GeneXpert arm (increased sensitivity in smear-negative cases) however, since this test is not as yet standard of care anywhere in the world it is considered ethical to randomize. There is no change to routine care in the control arm (except where culture is performed in addition during phase 1, which represents enhanced standard of care). The data generated from this study will be key to informing the cost/benefit analysis that we anticipate will motivate for the introduction of GeneXpert for the diagnosis of TB worldwide. This will represent a major advance in TB care and the single most important development in TB diagnostics in over 50 years.

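### The consent waiver rests on a statement of no risk, but the Phase 2 Xpert arm drops culture and drug susceptibility testing that standard practice allows, and the protocol's own figures show cases missed

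*Protocol*

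**What the plan says.** **Phase 2, Routine Arm.** The second sputum goes for microscopy, or for "microscopy plus culture +/- susceptibility testing (reference laboratory) at the clinic discretion (i.e., following standard practice"). The basis for treatment is given as "Treatment based on microscopy and/or culture results, as per routine practice".

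**Phase 2, Xpert Arm.** "Xpert negative cases will have no culture performed". The second sputum goes "for microscopy plus culture and DST if Xpert shows rifampicin resistance"; no other trigger for DST is named. Xpert-negative patients are told to come back if they do not improve, and no further test is specified.

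**Phase 1, Xpert Arm.** Every patient has a culture, and DST has two triggers: "DST performed if clinical suspicion of MDR-TB, or if Xpert test shows rifampicin resistance". The clinical-suspicion trigger does not reappear in the Phase 2 Xpert arm.

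**Abstract.** In the second of its three phases (Implementation), the reference laboratory cultures all cases.

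**Risk and consent.** Preparation and Participation of Health Services: "We have received ethics approval for waiver of informed consent, since there is no risk and substantial benefit for the patients". Ethical Considerations: "participation in this project poses no foreseeable risk to patients". That section also says that the routine algorithm is modified when Xpert is used and that Xpert "provides at least as good a diagnostic test as the current standard algorithm". It does not say that culture and DST are withdrawn from some patients.

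**The concern.** Take one patient, such as a re-treatment case or a symptomatic contact of a known MDR case (both are in the inclusion criteria), presenting in either of two adjacent Phase 2 weeks. In a Routine week the clinic may order culture and DST. In an Xpert week a negative Xpert closes off culture, and a rifampicin-sensitive Xpert closes off DST, at that presentation. The calendar week decides which applies, and the patient is not asked.

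If Xpert missed nothing, this would carry no risk. The protocol's own tables say that it misses some cases. The stated ground for not seeking consent is then inaccurate for exactly those patients whom the clinic would have cultured. The abstract makes this worse: anyone matching its phases to the Methods by order would believe that a culture stands behind every Phase 2 Xpert result. An inaccurate basis for a waiver cannot be repaired once patients have been enrolled under it.

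**Working it through.** **Inputs from the protocol**
- Xpert sensitivity in smear-negative, culture-positive TB: 90.0% (84.6% to 93.7%). For rifampicin resistance: 96.1% (92.4% to 98.0%). Both are in the section on clinical performance and come from three Xpert tests and four cultures per patient.
- Xpert tests per patient in this study: one (Sample size). The performance section says that a single result still performed well but gives no number.
- TB suspects: 45 to 50 per site per week (Sample size). Phase 2 lasts 16 weeks with weekly alternation, so 8 are Xpert weeks.

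**Not given:** the share *c* of Routine-arm patients sent for culture or DST. It is varied below from 0 to 100%.

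**Step 1: the plan's figures.** No numerators or denominators are stated, so the sensitivities cannot be recomputed from inputs. They are internally consistent: a Wilson 95% interval for 153/170 gives 90.0% (84.6% to 93.7%), and for 195/203 gives 96.1% (92.4% to 98.0%). These counts are back-solved, not stated.

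**Step 2: share missed = 1 − sensitivity.**
- Smear-negative, culture-positive TB: 100 − 90.0 = 10.0% (100 − 93.7 = 6.3% to 100 − 84.6 = 15.4%).
- Rifampicin resistance: 100 − 96.1 = 3.9% (100 − 98.0 = 2.0% to 100 − 92.4 = 7.6%).

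If a positive on any of the three tests counted as positive (an assumption about the source data), one test cannot miss fewer. How many more it misses cannot be derived here.

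**Step 3: diagnoses lost by withdrawing the discretionary test = *c* × share missed.** This takes the routine culture or DST as perfect, which errs on the high side.

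| Assumed uptake *c* | Lost per 100 smear-negative, culture-positive | Lost per 100 rifampicin-resistant |
|---|---|---|
| 0% | 0 | 0 |
| 25% | 2.5 (1.58 to 3.85) | 0.98 (0.5 to 1.9) |
| 50% | 5.0 (3.15 to 7.7) | 1.95 (1.0 to 3.8) |
| 75% | 7.5 (4.73 to 11.55) | 2.93 (1.5 to 5.7) |
| 100% | 10.0 (6.3 to 15.4) | 3.9 (2.0 to 7.6) |

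The loss is zero only if clinics never order these tests.

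**Step 4: the other side of the balance.** Per 100 smear-negative, culture-positive patients, the Xpert arm finds 90 and the Routine arm finds 100*c*. The difference, 90 − 100*c*, is +65 at *c* = 25%, +40 at 50%, +15 at 75% and −10 at 100%. The break-even point is *c* = 90% (84.6% to 93.7% over the interval).

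**Step 5: scale.** The Phase 2 Xpert arm has 8 × 45 = 360 to 8 × 50 = 400 patients per site. If 3% to 10% of suspects are smear-negative, culture-positive (an assumption), that is 360 × 0.03 = 10.8 to 400 × 0.10 = 40 cases. Xpert would find about 10 to 36 and miss about 1 to 4 (0.7 to 6.2 over the interval). The missed count is gross. It equals a loss against routine care only if every such patient would have been cultured.

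**The case against.** **The contrast is declared.** A reader might infer that the arms are confounded because they differ by more than the presence of Xpert. The documents do not support that. The hypothesis sets management on a single Xpert result against the conventional algorithm. Objective 1a names the local routine algorithm as comparator, and the evaluation-study section defines the arms as alternative bases for treatment. Gain from Xpert minus loss of discretionary culture is the net effect being asked about. This objection stands in full. Only the label matters: the effect is of replacement, not addition.

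**The claim of being at least as good is not refuted.** It compares algorithms overall, and Step 4 favours Xpert for smear-negative TB unless culture uptake exceeds about 90%. This also stands, so that sentence need not be withdrawn.

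**There are safeguards.** Phase 1 cultures every patient in both arms before Phase 2 drops culture, although no rule for proceeding is stated. Xpert-negative patients may return, and nothing bars later investigation. Xpert-positive patients are seen at 2 and 6 months. These reduce the consequence of a miss; they do not make it zero. The MTBDRplus confirmation reaches only results that Xpert already calls resistant.

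**Nothing was concealed.** The Phase 2 algorithm is in the protocol, and what else the ethics committee was told is unknown. That is fair, but the protocol's own risk statements remain absolute and omit the withdrawal.

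**The abstract may describe a different phase scheme.** It uses other phase names and durations, so the conflict depends on matching phases by order. It is nevertheless current text and should agree with the Methods.

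**Conclusion.** The point holds as a fault in the risk statement and in consistency, not as a flaw in the comparison. On the protocol's own figures, 10.0% (6.3% to 15.4%) of smear-negative, culture-positive TB and 3.9% (2.0% to 7.6%) of rifampicin resistance go undetected by Xpert. In the Phase 2 Xpert arm no culture or DST follows at that presentation. Unqualified statements of no risk, one of which is the stated ground for waiving consent, cannot stand beside those numbers.

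The rates rest on three tests per patient; the rate for the single test used here is unknown. The loss relative to routine care scales with an uptake that the protocol does not state.

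A reader might go further and infer that the Xpert arm harms patients on balance. The documents do not show that, and average detection may well be better. The conclusion concerns the individual who would have been cultured under standard practice, and what was said to justify not asking that individual.

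**What to change.** Reconcile the Abstract, the two Phase 2 arm descriptions, Preparation and Participation of Health Services, and Ethical Considerations on one question: are culture and DST available in the Phase 2 Xpert arm, and on what trigger? Which rule should apply is for the sponsor and investigators, not for this review.

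If the withdrawal is intended:
- replace both statements of no risk with one saying that discretionary culture and DST are withdrawn in that arm, that the tabulated miss rates apply to three tests, and that the rate for one test is not given;
- notify the ethics committee, so that the waiver rests on an accurate statement;
- describe the Phase 2 effect as Xpert in place of discretionary culture and DST;
- report culture and DST use, and the cases found through them, by arm. The case report form already records how and when TB and drug resistance were diagnosed and which further investigations were done, so no new data collection is needed.

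The cost is protocol wording, an ethics notification and a less favourable risk statement. The design, sample size and primary comparison are unaffected.
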